## Abstract

**Background:**

The prevalence of type 2 diabetes is increasing in epidemic proportions in low- and middle-income countries. There is an urgent need for novel methods to tackle the increasing incidence of diabetes. The ubiquity of mobile phone use and access to Internet makes mobile health (mHealth) technology a viable tool to prevent and manage diabetes.

**Objective:**

The objective of this randomized controlled trial is to implement and evaluate the feasibility, cost-effectiveness, and sustainability of a reality television–based lifestyle intervention program. This intervention program is delivered via a mobile phone app (mDiab) to approximately 1500 Android smartphone users who are adults at a high risk for type 2 diabetes from three cities in India, namely, Chennai, Bengaluru, and New Delhi.

**Methods:**

The mDiab intervention would be delivered via a mobile phone app along with weekly coach calls for 12 weeks. Each participant will go through a maintenance phase of 6 to 8 months post intervention. Overall, there would be 3 testing time points in the study: baseline, post intervention, and the end of follow-up. The app will enable individuals to track their weight, physical activity, and diet alongside weekly video lessons on type 2 diabetes prevention.

**Results:**

The study outcomes are weight loss (primary measure of effectiveness); improvement in cardiometabolic risk factors (ie, waist circumference, blood pressure, glucose, insulin, and lipids); and improvement in physical activity, quality of life, and dietary habits. Sustainability will be assessed through focus group discussions.

**Conclusions:**

If successful, mDiab can be used as a model for translational and implementation research in the use of mHealth technology for diabetes prevention and may be further expanded for the prevention of other noncommunicable diseases such as hypertension and cardiovascular diseases.

**Trial Registration:**

Clinical Trials Registry of India CTRI/2015/07/006011 http://ctri.nic.in/Clinicaltrials/pdf_generate.php? trialid=11841 (Archived by WebCite at http://www.webcitation.org/6urCS5kMB)

## Introduction

The International Diabetes Federation estimates the global prevalence of type 2 diabetes mellitus (T2DM) to rise to 642 million by 2040 from the current number of 415 million [1]. Three-fourths of this population lives in the low- and middle-income countries (LMICs) such as India [1-3]. Studies in different populations have shown that a large part of T2DM is attributed to factors such as obesity (both generalized and abdominal), sedentary lifestyle, and poor diet [4-7]. Anjana et al [8] assessed the population attributable risks in an urban Indian population and reported that by modifying just two factors, namely, diet and physical activity, up to 50% of new onset T2DM can be prevented.

Several randomized controlled trials (RCTs) carried out on primary prevention of T2DM have shown that lifestyle modification and metformin therapy can reduce the incidence of T2DM in people who are in the prediabetes stage, that is, those having impaired glucose tolerance (IGT) or impaired fasting glucose (IFG), or both [9-16]. However, most of these trials were conducted face to face. This involves a lot of man power, cost, and time. The question arises whether similar results can be obtained using modern technology without the need for face-to-face interaction.

The World Health Organization (WHO) considers mobile health (mHealth) as a component of electronic health (eHealth). The definition of eHealth according to the WHO is “the use of information and communication technologies for health,” and mHealth is defined as “medical and public health practice supported by mobile devices, such as mobile phones, patient monitoring devices, personal digital assistants (PDAs), and other wireless devices” [17].

It is of interest to note that India stands second worldwide both in the prevalence of type 2 diabetes [1] as well as in the number of mobile phone users [18]. According to the statistics provided by the Telecom Regulatory Authority of India, the number of wireless telephone users in India increased from around 1034 million in April 2016 to around 1174 million in January 2017, that is, 100 million users added within a year [19]. Moreover, the Internet and Mobile Association of India (IAMAI) and Indian Market Research Bureau (IMRB) statistics have also shown that India has the second largest population using the Internet, of which a large number gain access to the Internet using their smartphones. The IAMAI and IMRB prediction for the mobile-based Internet users is that there would be 371 million users by June 2017 from 306 million in December 2016, which represents an increase of 21% in just 6 months [20]. This massive upswing and uptake of technology in the field of mobile technology renders mHealth as a liable opportunity to provide individual-level support beyond traditional clinic-based care technology [17,20-24].

With this background information, we took up a trial of primary prevention of diabetes based on mHealth. The aims of this trial are to understand the feasibility, cost-effectiveness, and sustainability of a reality television–based lifestyle intervention delivered via a mobile phone app along with the support of a health coach for 12 weeks and to evaluate its effect on weight loss, cardiometabolic risk factors, and behavioral and social variables, such as physical activity, quality of life (QOL), and adoption of healthier diet and lifestyle behaviors, in Android mobile phone users who are at a high risk of developing T2DM.

## Methods

### Study Design and Participants

This study is an RCT being conducted at three cities in India (Chennai, Bengaluru, and New Delhi) between 2016 and 2018. Android mobile phone users, between the age groups of 20 and 65 years, are screened for eligibility based on a combination of screening criteria detailed in Figure 1. The rationale for choosing Android users is based on the data published in 2016 that 97% of the mobile phone users in India use the Android operating system [25]. This figure rose from 90% in 2015 [25].

### Eligibility Criteria

The screening criteria are designed to ensure that individuals at a high risk of developing diabetes are selected for the study. To select the high-risk group, a combination of the Indian Diabetes Risk Score (IDRS), body mass index (BMI), and capillary blood glucose (CBG) is used.

**Figure 1 figure1:**
[figure not shown]
Eligibility criteria at screening and baseline. IDRS: Indian Diabetes Risk Score; BMI: body mass index.

IDRS is a simplified and validated tool that uses 4 parameters, namely, age, abdominal obesity, family history of diabetes, and physical activity [26,27]. It was shown that a high IDRS score increases with the risk of T2DM, metabolic syndrome, and cardiovascular disease [28]. Generally, an IDRS score of 40 indicates a moderate risk of developing diabetes and a score of 60 indicates a high risk. For the purpose of including a wide range of high-risk population, we classified an IDRS score of ≥40, along with either a BMI indicative of obesity or CBG indicative of prediabetes (IFG=100-125 mg/dL or IGT=110-199 mg/dL) to determine eligibility at screening. However, an IDRS score of ≥60 is considered as an independent criterion to determine eligibility. BMI is an important diagnostic marker for overweight and obesity [29]. We set a cut point of ≥23 kg/m^2^to indicate overweight and obesity as defined by the WHO Asia Pacific guidelines [30], and this is used in combination with CBG, indicating prediabetes and/or and an IDRS ≥40. However, a BMI ≥25 kg/m^2^ is considered as an independent criterion to determine eligibility. The CBG testing is used to identify an IFG of 100 to 125 mg/dL or an IGT of 110 to 199 mg/dL at screening using the WHO cut-offs [31]. The final eligibility criterion for entry into the trial is defined as either an IFG of 100 to 125 mg/dL and/or an IGT of 140 to 199 mg/dL through a 75-g oral glucose tolerance test and/or a BMI ≥25 kg/m^2^, indicating obesity at baseline (Figure 1).

The exclusion criteria for the study are participants who are pregnant or breastfeeding, are involved in other wellness programs, whether they have been previously diagnosed with diabetes or have a history or evidence of heart disease or any other serious illness, are children or young people (ie, aged <20 years) or older adults (ie, aged >65 years), or have conditions (such as orthopedic conditions) that would impede participation in this study.

### Recruitment

Recruitment is carried out through screening camps at clinic settings, corporates/worksites, residential colonies/gated housing complexes, educational institutions, religious or spiritual institutes, open public spaces, and direct referrals (such as participants referred by study staff and physicians) to cover the general population at large.

If an individual fulfilled 1 or more of the criteria enlisted in Step 1 (Figure 1), they are invited for baseline testing, and each participant is subjected to a panel of tests as detailed in Table 1 to ensure final eligibility into the study (Step 2 in Figure 1). At each site, approximately 3000 people are screened based on the screening criteria shown in Figure 1, and approximately 1000 individuals would be available for baseline testing. The main aim of the baseline visit is to ensure that the individuals screened do not have type 2 diabetes [31] or fall under any other exclusion criteria and that they have understood the requirements of the intervention study. A summary of measures that are conducted at each visit are detailed in Table 1 and Multimedia Appendix 1.

**Table 1 table1:** Summary of study measures.

Measurements		Screening	Baseline	Post intervention	End of follow-up
**Questionnaires**					
	Short questionnaire	✓			
	Questionnaires measuring participants’ health habits, diet behavior, quality of life, health-related costs, and physical activity/inactivity		✓	✓	✓
**Anthropometry**					
	Weight (in kg)		✓	✓	✓
	Height (in cm)		✓	✓	✓
	Waist circumference (in cm)	✓	✓	✓	✓
	Body fat (%)		✓	✓	✓
	Blood pressure		✓	✓	✓
	Indian Diabetes Risk Score	✓			
**Biochemical parameters**					
	Capillary blood glucose	✓			
	Venous fasting blood glucose		✓	✓	✓
	Postglucose load (2 hours)		✓		✓
	Fasting insulin assay		✓	✓	✓
	HbA1c		✓	✓	✓
	Lipid profile		✓	✓	✓

### Randomization

A study staff not involved in the study randomizes the participants into the intervention and control group across sites by the random allocation sequence method using a random numbers table. The randomization grid, which contained only the study unique ID number and inclusion criteria variables, is filled at each site by the site coordinators and sent to the personnel at the central randomization site as per the weekly randomization schedule. The grids are sent back to the sites post randomization. Therefore, the study personnel randomizing the participants are blinded to the group allocation of the participants, whereas the study team and participants at each site are not.

### Control Group

The control group participants receive usual care for patients with prediabetes or obesity at all the 3 study sites. They meet a nutritionist once after randomization and receive handouts reinforcing prevention of T2DM through increased physical activity and weight loss. All control group participants are offered access to the app at the end of the study.

### The Mobile App Description

An mHealth app called *mDiab* is used by all intervention group participants. mDiab has 12 weeks of video lessons that were created based on the Diabetes Community Lifestyle Improvement Program (D-CLIP) lessons and experiences [16], which in turn were originally developed using the US Diabetes Prevention Program. The video lessons are in the form of a reality television show, where real actors role-play and enact the concepts of lifestyle behavior change. This inspires and motivates the participants viewing the video lessons in the app to change their lifestyles to improve their health. For example, for the video lesson on incorporating a healthy diet, the actors act out ways to help the participant understand the concept and share experiences on the challenges faced while adopting it in real life. They also help in overcoming the challenges by suggesting suitable solutions. Apart from the video lessons, the app also has goal setting, alerts, and small text modules, which are brief write-ups on the video lessons. There are also multiple-choice questions to help reinforce learning. The 12 weeks of video lessons cover various aspects of T2DM prevention, with the goal of reducing diabetes risk through weight loss of at least 5%. The contents of the video lessons are described in Table 2 and Multimedia Appendix 2. Overall, the app has 3 important components—the video lessons as described above, tracking of behaviors, and weekly calls by the health coaches.

#### Tracking

This feature of the app is meant to enable users to track their diet, physical activity, and weight. The calorie and fat goals provided are based on the D-CLIP study. The participants are encouraged to track their daily food intake. The food database is developed using the [name] Food Atlas [32] and National Institute of Nutrition’s guidelines [33]. The activity tracker automatically counts the number of steps using the mobile phone’s inbuilt accelerometer sensor. Additionally, the participant is encouraged to add any specific activity he/she likes to do. The weight tracker sets an initial weight loss goal of 5% and enables tracking. Every participant in the intervention group receives a weighing scale as an incentive to enable them to track their weight. The app sends out standardized reminders and motivational messages according to the progress of each user. Screenshots of the app’s tracking features are shown in Figure 2 for better understanding.

#### Communication With the Health Coach

Health coaches in the mDiab program are trained nutritionists who call participants once a week to inform them about the objectives of the video lessons and their progress and finally email them with a progress report using the data tracked by the respective participant. The participants also have the opportunity to communicate with the health coaches in any case via a message tool inbuilt in the app, and the health coaches respond to the participants in 24 hours.

### Procedures

#### Data Collection

At screening, the participant’s basic demographic details, IDRS, and CBG are measured. Post that, the study has a total of 3 testing time points including baseline, post intervention, and end of follow-up. All testing visits (except screening) occur after an overnight fast of at least 8 to 10 hours. The study participants are administered a questionnaire to record their sociodemographic data at baseline. Changes in diet and frequency of consumption of common foods are assessed using a 3-day diet recall, and short validated food frequency questionnaires are administered at all visits. Mobile phone usage and mHealth efficacy are also assessed at all visits. Physical activity and exercise behaviors are recorded using the short Madras Diabetes Research Foundation Physical Activity Questionnaire (MPAQ). MPAQ is a reproducible and validated instrument that captures data from multiple activity domains (including sedentary activity) over a period of a year from adults of both genders and varying ages from various walks of life, residing in India [34]. The participant’s QOL is assessed using the WHOQOL-BREF instrument comprising 26 items [35]. It measures 4 broad domains: physical health, psychological health, social relationships, and environment. We also aim to assess the cost-effectiveness of using the mHealth intervention by assessing the incremental costs and benefits per quality-adjusted life-year (QALY). The cost-effectiveness of the mHealth intervention from an individual and collective perspective is compared with usual care by conducting incremental cost-effective analyses in which the net costs and net effectiveness of the mHealth intervention and the usual care are calculated and expressed as a ratio. All analyses are within the time frame of the trial. The direct medical and nonmedical costs/indirect costs associated with the mHealth intervention over 10 to 12 months are included in the cost-effectiveness [36]. Program adherence is measured by monitoring how well the participants used the various features of the app by responding to reminders and alerts. This is tracked using a Web-based dashboard. A 75-g glucose tolerance test [37] at 0 and 120 min along with blood tests for insulin, glycated hemoglobin (HbA1c), and lipids are conducted at baseline and at the annual follow-up visit.

**Table 2 table2:** *mDiab* overview of video lessons.

Sessions (Weekly)	Objectives
Session 1: Importance of self-monitoring	Effective and daily tracking using the habits program
	The importance of breakfast as a wholesome and balanced meal, along with sample meal plans
	How one can be in charge of their health beyond all daily challenges, including overloaded work schedule, trials of family life, involved social life, and healthy lifestyle changes
	Plan one’s day by planning the right time for eating
	Being true to oneself and achieving success
	Sleeping well for a healthy lifestyle
	Staying on track during the weekend
	Rewarding oneself
Session 2: Fat and calorie detective	Learning how fat and calories can affect health
	Learning where to find them in food
	Importance of portion sizes and measurement of food
	Being aware of fattening foods and hidden fats and switching to low-fat options to improve health and alleviate the risks of heart disease and diabetes
	Practicing being more aware and choosing food items consciously with lesser calories and fats, dwelling more into measuring foods
	Understanding that correlating the quantity of food eaten to its nutrient contribution (calories and fats) helps to remain within the fat and calorie limit for the day that is predetermined by one’s initial weight
	Using one’s skills to ration portions and choose food items judiciously by evaluating the consolidated caloric intake for the day; trying to find a balance through food and exercise
	Incorporating physical activity into your lifestyle
Session 3: Having a balanced meal	Understanding the importance of taking a balanced meal and learning what it looks like
	Getting the relevance of the “My plate” concept
	Understanding what it is to eat from different food groups
	Learning the good side of everything, especially fats
	Understand the balance between calories in and calories out by tipping the calorie balance and understanding the food serving sizes
Session 4: Being active	Techniques to make physical activity fun
	The FITT principle to balance your activity
	Exercises—leg raises and back extensions
	Reviewing what was learnt and putting it to practice
	Understanding the serious threat of sedentary lifestyle and keeping a track of F—frequency, I—intensity, T—type of activity, and T—time
Session 5: Learning about ourselves	Keeping food and activity cues by simplifying them to one’s core problems
	Learning how our environment causes us to be unhealthy
	Becoming aware of temptations that might steer one off course
	Steps to problem-solving
	Singling out areas in need of improvement and creating an action plan focusing on making these changes gradually
	Use tracking to one’s advantage
Session 6: Strategies for eating out	The healthy side of eating out
	Learning how to control what you eat when not at home
	Ordering healthy
	Planning ahead when going out to eat with friends or family
Session 7: Managing slip-ups	Managing and dealing with slip-ups
	Identifying the reasons for a slip-up
	Identifying negative thoughts and learning how to manage them
	Stretching exercises and learning some seated stretching techniques
	Understanding common external triggers for mismanaging diet and exercise and dealing with them
Session 8: Understanding social cues	Understanding social cues and how they affect us
	Making lifestyle changes using social cues to one’s advantage
	Being aware of your social interactions and how they affect you
	Learning to positively affect outcomes of unhealthy social cues
Session 9: Improving strength and flexibility	Improving strength and flexibility
	Strengthening one’s exercise program and learning resistance training
	Standing up for your health
	Incorporating strength training into your activity routine
Session 10: Volumetrics and eating mindfully	Understanding the importance and concept of volumetrics and eating mindfully
	High volume, low calorie foods—learning to eat more food that has fewer calories
	Eating mindfully by perceiving your physical and mental state
	Thinking before eating and being aware how one eats
	Paying attention to size, smell, texture, taste, and its other qualities
	Enjoying one’s meal to its fullest
Session 11: Stress management and staying motivated	Maintaining the momentum
	Recognizing positive lifestyle changes made so far
	Stress management
	Combating stress with planned activity or a healthy session of yoga
Session 12: Long-term heart health	Nurturing your heart into a healthy heart
	Understanding the importance of reducing risk of heart diseases by adopting positive lifestyle changes
	Understanding the importance of the new habits you have developed Using your skills to successfully keep the new habits you have created
	Keeping a schedule—tracking your new skill

**Figure 2 figure2:**
[figure not shown]
mDiab app screenshots.

At the post-intervention visit (3rd-month visit), fasting glucose, insulin, HbA1c, and lipids are measured. Height is measured at baseline visit, and anthropometry (height, weight, waist circumference, and body fat) and clinical measures (blood pressure) are measured at baseline, post intervention, and end of follow-up visits.

#### Program Acceptability

Program acceptability is assessed through focus group discussions (FGDs) with the intervention group participants at the end of follow-up. We plan to organize 2 FGDs at each site consisting of at least eight participants each. Thus, a total of 6 FGDs will be conducted in the study. The participants will be encouraged to share their experience on the benefits and problems of the intervention, financial worth of the program, and suggestions, if any, for improvement. Participants who drop out will also be contacted to understand their reasons for dropping out and to obtain their feedback.

#### Sample Size Calculation

Our study randomizes 1500 individuals across 3 sites to receive either the mHealth diabetes prevention program or usual care with a 6-month maintenance period. Considering an obesity prevalence of 20% as reported in the Indian Council of Medical Research-India Diabetes (ICMR-INDIAB) study [38,39] and with south Asians having a low BMI threshold compared with the rest of the population, 5% weight loss was determined as the primary outcome in the intervention group. On the basis of this assumption, a sample size of 588 individuals in each arm will be required to obtain a minimum of 3% difference in weight loss between groups with a power of 80% and a significance level of 5%. As this is a mobile phone–based intervention study, expecting a slightly higher dropout rate of 25%, 735 individuals in each group will need to be tested in the trial, resulting in a total of 1470, which has been rounded off to a total of 1500 individuals across 3 sites (500 per site).

All sample size and power calculations were done using the OpenEpi (The OpenEpi Project, Version 3, Atlanta, Georgia).

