#### Statistical Analysis

Quantitative analyses of the obtained data will be conducted in STATA (StataCorp, Version 15, College Station, Texas) and SPSS (IBM SPSS Statistics for Windows, Version 24.0. Armonk, NY). A probability of <0.05 will be considered statistically significant for all tests. Effectiveness of the intervention will be assessed by measuring the differences in the study arms in terms of the primary outcome, weight loss and secondary outcomes, behavioral and social variables, and cost-effectiveness. Continuous variables will be assessed for normality, and anomalous values will be categorized. All variables will undergo descriptive analyses. *t* tests will be used to compare between the 2 groups. Data will be presented before and after adjusting for confounders. Qualitative data include analyses of the audiotaped transcripts from the FGDs. The transcripts will be de-identified, and textual data will be extracted from the same. Following this, key themes will be identified and reported.

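### The figure of 588 per arm reproduces as a two-proportion calculation (5% vs 2%), which does not match a weight-loss outcome compared by t tests

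*Protocol article*

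**What the plan says.** The Sample Size Calculation section gives the target and the number together: "a sample size of 588 individuals in each arm will be required to obtain a minimum of 3% difference in weight loss between groups". Power is 80% and significance 5%; sidedness is not stated. The same section says that "5% weight loss was determined as the primary outcome in the intervention group". It opens its reasoning with a population rate: "Considering an obesity prevalence of 20% as reported in the Indian Council of Medical Research-India Diabetes (ICMR-INDIAB) study". After an allowance for 25% dropout, "735 individuals in each group will need to be tested in the trial", and the total is rounded to 1500. No SD, control-arm value, responder rate or formula is printed.

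Two other places describe the outcome and its analysis. The Abstract (Results) lists "weight loss (primary measure of effectiveness") with no responder definition. The Statistical Analysis section again names weight loss as the primary outcome and plans t "tests will be used to compare between the 2 groups". The mobile app description uses 5% as a weight-loss goal for participants, not as an endpoint definition.

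**The concern.** A t test on weight loss compares means, so its sample size depends on the difference in means and on an SD. A two-proportion calculation depends on the share of participants with an event in each arm. The 5% and 3% here are worded as amounts of weight loss. If they were entered as shares of participants, the printed sample size and power answer a different question from the one that the analysis will ask.

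This is the only power statement for the primary outcome. Depending on which endpoint is meant, the trial is either much larger than its stated target requires or, at responder rates higher than those that reproduce 588, well short of 80% power for the same gap. In either case a reader cannot take the statement of 80% power for 3% at face value.

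**Working it through.** **Inputs from the article:** 588 per arm; 80% power; 5% significance; 5% in the intervention arm; 3% difference; equal arms; 25% dropout; 1500 randomized. **Implied:** 5% − 3% = 2% in the control arm. **Not in the article, assumed below:** two-sided testing, SD of percent weight loss, responder rates.

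**1. Reproducing 588.** Two proportions, pooled variance under the null, no continuity correction:

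n = [1.960·√(2p̄(1−p̄)) + 0.842·√(p₁(1−p₁) + p₂(1−p₂))]² / (p₁−p₂)²

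With p₁ = 0.05, p₂ = 0.02 and p̄ = 0.035:

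- first term: 1.960 × √0.06755 = 0.5094
- second term: 0.842 × √0.0671 = 0.2180
- n = 0.7274² / 0.0009 = 587.9, so 588.

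Variants of the same pair miss: 653 with continuity correction, 586 unpooled, 463 one-sided. Among whole-percent pairs 3 points apart, with the lower rate from 0% to 59%, only 5% versus 2% comes close to 588. The 20% prevalence does not lead there either: 20% versus 17% gives 2629 and 20% versus 23% gives 2943.

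**2. The calculation that matches a t test.** Two means, difference 3 percentage points:

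n = 2·SD²·(1.960 + 0.842)² / 3² = 2·SD² × 7.849 / 9

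| Assumed SD (points) | n per arm |
|---|---|
| 4 | 28 |
| 5 | 44 |
| 6 | 63 |
| 8 | 112 |

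Solving for the SD that gives 588: √(588 × 9 / 15.70) = 18.4 points. At 588 per arm, power for 3 points is above 99.9% for any SD from 4 to 8.

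**3. What 1500 would deliver on that reading.** 750 × 0.75 = 562.5, so about 562 evaluable per arm. Difference detectable at 80% power = 2.802 × SD × √(2/562):

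- SD 4: 0.67 points
- SD 8: 1.34 points

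The 95% confidence interval half-width, 1.96 × SD × √(2/562), is 0.47 points for SD 4 and 0.94 points for SD 8.

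**4. The responder reading.** Suppose the endpoint is the share losing at least 5% of body weight. By step 1, 588 per arm has 80% power for 5% versus 2%. For the same 3-point gap at other assumed control rates:

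| Control vs intervention | Power at 588 per arm | n per arm for 80% |
|---|---|---|
| 5% vs 8% | 55% | 1059 |
| 10% vs 13% | 36% | 1774 |
| 20% vs 23% | 24% | 2943 |

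**The case against.** **The formula is inferred.** The article prints none and never gives 2%. A calculation in kilograms could also reach about 588: 3% of an assumed 70 kg is 2.1 kg, which needs an SD of about 12.9 kg. That route requires two figures the article does not give, while 5% versus 2% requires nothing beyond the article's own numbers and the usual defaults. The inference is strong, but it should be called one.

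**The endpoint is ambiguous.** The sentence naming 5% weight loss as the primary outcome can be read as a responder endpoint, and the t-test sentence is general. On that reading a two-proportion formula is the right type, and 80% power is correct for 5% versus 2%. A reader might infer that 588 fits no possible endpoint; that goes too far. What stands is that these rates are neither stated nor justified, and that the analysis section still points to a comparison of means.

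**Extra precision does no harm.** A reader might also infer that a null or small result could not be interpreted against 3%. The arithmetic says otherwise: half-widths of about 0.5 to 0.9 points allow a clear comparison. Nor can the trial be called underpowered outright, since that holds only for a responder endpoint at assumed higher rates with the gap held at 3 points.

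**The 20% prevalence** can be read as background for choosing a 5% goal rather than as a term in the formula, so its absence from the arithmetic is not in itself an error. The next sentence, however, presents 588 as resting on this reasoning.

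**A condensed article may leave the SD elsewhere.** That is fair, and its absence is not the point. The point is that the printed number, power and target do not fit the printed outcome and test unless the SD is about 18 points.

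**Conclusion.** The point holds. The sample size and 80% power in the Sample Size Calculation section do not match the outcome and tests named in the Abstract and the Statistical Analysis section.

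On the reading those two sections favour, mean percent weight loss, power for 3 points is far above 80%, and the trial can reach significance at well under half the stated target. This rests on an assumed SD of 4 to 8 points. On the responder reading the stated power is right for one unstated pair of rates, and much lower at the other rates examined. The size of that shortfall rests on assumed control rates of 5% to 20% and an unchanged 3-point gap.

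The documents do not settle which endpoint was intended, and nothing here calls for a different number of participants.

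**What to change.** Keep 1500. Then:

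- State one primary endpoint in the same words in the Abstract, the Sample Size Calculation section and the Statistical Analysis section. Given the planned t test, percent weight change from baseline is the natural choice.
- Replace the statement of 588 per arm at 80% power with a calculation of the matching type, giving a sourced SD. If a responder endpoint is kept instead, give and justify both arms' rates and plan a test of proportions.
- Restate the difference detectable with the expected evaluable number. For percent weight change with about 562 per arm this is roughly 0.7 to 1.3 points if the SD is 4 to 8.
- Keep 3% as the target difference and judge the confidence interval against it, so that a significant but smaller difference is not presented as meeting the target.
- Leave the 20% obesity prevalence as background if wanted, but do not present it as the assumption behind 588.

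The cost is one rewritten paragraph and aligned endpoint wording in two other places, with no change in enrolment.

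### The 25% dropout allowance is applied as 588 × 1.25 instead of 588 / 0.75, so 1500 randomised leave about 562 evaluable per arm, not the 588 the plan requires

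*Protocol article*

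**What the plan says.** The whole derivation is in the Sample Size Calculation section of the protocol article. It states that "a sample size of 588 individuals in each arm will be required" and gives the target as "to obtain a minimum of 3% difference in weight loss between groups", with 80% power and a 5% significance level. It then makes an allowance for attrition, which it expects to be somewhat higher because the intervention is delivered by mobile phone: "expecting a slightly higher dropout rate of 25%, 735 individuals in each group will need to be tested in the trial". The last step is "resulting in a total of 1470, which has been rounded off to a total of 1500 individuals across 3 sites", which is 500 per site. The same section opens by giving 1500 as the number randomised. No other section of the article revises these figures.

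**The concern.** The dropout step runs in the wrong direction. Adding 25% to the number needed at the end is not the same as enrolling enough people that 588 per arm remain after 25% have left. The section states a required number, a dropout rate and an enrolment figure together, and the three do not fit. A reader who takes the paragraph at face value would believe that the trial keeps 80% power at the dropout rate the sponsor itself expects. It does not quite do so, and the final rounding to 1500 does not repair it.

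**Working it through.** **Inputs, all from the Sample Size Calculation section.** Required per arm 588; dropout 25%; inflated number 735 per arm; total 1470, rounded to 1500 (750 per arm with equal arms); power 80%; significance level 5%.

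**Step 1. Reproduce the plan's figure.**
588 × 1.25 = 735, an exact match, and 2 × 735 = 1470. The plan therefore added 25% of the evaluable number.

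**Step 2. Apply the allowance correctly.**
Enrolled per arm = required / (1 − dropout) = 588 / 0.75 = 784. Total = 2 × 784 = 1568, about 523 per site. This is 1568 − 1500 = 68 more than planned, and 68 / 1568 = 4.3%.

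**Step 3. What the 1500 deliver at 25% dropout.**
750 × 0.75 = 562.5, so about 562 per arm. The shortfall is 588 − 562.5 = 25.5, about 25 per arm. In total, 1500 × 0.75 = 1125 against 2 × 588 = 1176.

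**Step 4. The dropout that 1500 can bear.**
1 − 588 / 750 = 0.216, or 21.6%. The unrounded 735 per arm would bear 1 − 588 / 735 = 0.20, or 20%.

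**Step 5. Power at 562 per arm, without assuming how 588 was derived.**
With everything else fixed, the standardised effect scales with the square root of n:

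power = Φ[(1.960 + 0.842) × √(562 / 588) − 1.960]

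√(562 / 588) = 0.978, and 2.802 × 0.978 − 1.960 ≈ 0.779. Φ(0.779) = 0.782, so power is about 78.2%, a loss of about 1.8 points. This uses a two-sided 5% level; the article does not state sidedness.

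**Step 6. Cross-check on an inferred basis.**
The section gives 5% for the intervention arm ("5% weight loss was determined as the primary outcome in the intervention group") and a difference of 3%, but no comparator value. If the comparator is taken as 5% − 3% = 2%, a two-sided comparison of two proportions with pooled variance and no continuity correction gives

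n = [1.960 × √(2 × 0.035 × 0.965) + 0.842 × √(0.05 × 0.95 + 0.02 × 0.98)]² / 0.03² = 588.

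This reproduces the plan's 588. On that basis power is 80.0% at 588 and 78.2% at 562, the same as in step 5. The 2% and the two-sided test are inferences from this match and are not stated in the article. Steps 1 to 4 do not depend on them.

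**The case against.** The strongest case on the other side is that the slip has little practical effect. The trial randomises 1500, so 562 per arm is the operative number and the loss is about 1.8 points of power. Nothing about the estimand or the type I error changes. That stands, and it settles the severity. For the same reason the result for the unrounded 1470 (735 × 0.75 = 551 per arm, power 77.4%) should not be used to describe the trial; it belongs to a trial that is not being run.

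One could also read the 25% as the ratio of dropouts to completers, so that 147 of 735 are lost and 588 remain. That is a 20% loss, and the section calls the 25% a dropout rate, so this reading does not hold.

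Two stronger inferences are tempting, and the document supports neither:

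- **That the trial is materially underpowered, or must enrol 68 more.** The Statistical Analysis section plans t tests on weight loss, and no standard deviation is given. Purely as an assumption, a standard deviation of 5 to 10 percentage points of weight change would need about 44 to 175 per arm for a 3-point difference. The standard deviation would have to be about 18 points before 562 per arm fell short of 80% power.
- **That no extra enrolment is needed because the outcome is continuous.** This depends on the same missing standard deviation, so it cannot be asserted either.

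Whether 588 suits the planned t test is a separate question. It does not alter the dropout arithmetic.

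**Conclusion.** The arithmetic is wrong as written, and nothing else in the article corrects it. On the plan's own 588 and 25%, the inflated number is 784 per arm, not 735. The 1500 randomised fall about 25 evaluable participants per arm short of the stated requirement. The shortfall rests only on those figures and on equal arms. The power of about 78% also takes the stated 80% at 588 as given and assumes a two-sided test. A reader should not treat 5% versus 2% as the plan's stated basis; it is inferred because it reproduces 588. This is a minor arithmetic correction: the stated power and the stated dropout rate cannot both hold at 1500, but the gap is small.

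**What to change.** Keep 1500 and restate the paragraph along these lines: 1500 randomised with 25% dropout gives about 562 evaluable per arm and about 78% power on the stated basis; 80% power (588 per arm) is kept only if dropout is at most 21.6%. In the same place, correct the inflated figure for 588 evaluable to 784 per arm, 1568 in total. Do not add a claim that enrolment is sufficient on a continuous-outcome basis unless a standard deviation is stated and the calculation shown. The cost is a sentence or two and a slightly less favourable stated power; recruitment is unchanged.
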